## Appendix Q: Adverse Event Form

**YUSH COVID-19 PATIENT PROTOCOL 2020**

**ADVERSE EVENT FORM**

PATIENT NO: ________________PATIENT INITIALS :_____________DATE:____________________

**Adverse Event Term:** _____________________________________________________________

| AE Serious | □ Yes □ No | |
| --- | --- | --- |
| Start Date______________________ End Date ___________________Ongoing□ Yes □ No | | |
| Related to study treatment : Ashwagandha | | □ Yes □ No |
| Related to study treatment – Hydroxychloroquine | | □ Yes □ No |
| Related to study Procedures | | □ Yes □ No |
| Action taken with study treatment : Ashwagandha  Dose not changed □; Drug Interrupted □; Drug Withdrawn□; Not Applicable □ | | |
| Action taken with study treatment: Hydroxychloroquine  Dose not changed □; Drug Interrupted □; Drug Withdrawn□; Not Applicable □ | | |
| Other Action taken :None □; Medication required □; Other Treatment Required □; Permanent Study discontinuation □ Details of treatment/medication: _________________________________________________________________________________ | | |
| AE toxicity Grade: Grade 1 □; Grade 2 □; Grade 3 □; Grade 4 □ | | |

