# 14. SAFETY ISSUES AND ENDPOINTS, ADVERSE EVENTS

All adverse events will be recorded and meticulously followed till resolution. Serious adverse events will require immediate action and further communication by the study investigator. AE will be classified by the study physician as described in Appendix P and classified as shown in Appendix Q and recorded in the AE form by the investigator along with its grading (Appendix R).

A-priori check list of common drug related side as a ready reckoner will be provided to all investigators so that timely action may be taken if a patient reports any kind of adverse event that may be related to the study intervention. The patients will be encouraged to record any kind of symptom that they may think is due to a drug in their personal diary which will be scrutinized by the study physician at monthly visits and on completion.

The following ‘**Stop rules’** will be applied to withdraw the patient prematurely because of safety concerns:

1. Patients developing severe COVID-19 as described above under the ‘exclusion criteria’
2. Requiring hospitalization for disorders other than COVID-19 will be critically evaluated by the study physician to decide continuity in the study
3. Any adverse clinical or lab profile that in the opinion of the investigator is likely to be due to therapeutic intervention and threatens to deteriorate the wellbeing of the patients

Data Safety Monitoring Board (DSMB) will be established to monitor safety of the participants and assess safety data. The CONSORT extension for HARMS will be used to document and report safety data.

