# 19. ADMINISTERATIVE ISSUES

**19.1 Study Documents**

A Patient Information Sheet (see Appendix H) will be handed over to each patient participant in an easy to understand question answer format and in the language best understood.

Only the patient’s initials / ID number will be used for identification in the study records and database.

Study confidentiality will be maintained. The following documents will be used in the study:

- Patient Case Record Forms (CRF): This will be provided for each study participant. All centers must follow instructions for filling of CRF that have been listed in the beginning of each CRF file.
- Informed Consent in the regional language best understood by the study participant.
- Adverse Event Form
- Serious Adverse Event Form
- Termination Form
- Medication Log
- WHO- Quality of Life

All the centers will be provided with a file in which to organize and retain all study-related documents. All study correspondence should be filed by the investigator in this file. The Site Master File will be available for inspection by the individual monitoring the study in order to ensure that all the relevant documents are present and easily retrievable.

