## Appendix N: Self-Reported Questionnaire

**AYUSH COVID-19 PATIENT PROTOCOL 2020**

**SELF REPORTED QUESTIONNAIRE**

PATIENT NO: ________________PATIENT INITIALS :_____________DATE:____________________

1. Do you feel Feverish? □ Yes □ No
2. Do You have sore throat □Yes □No
3. Do you have Nasal stuffiness/Sneezing/Runny Nose? □Yes □No
4. Do You have Cough □Yes □No
5. Did you Suffer from any symptom that could be due to the study drug □Yes □No

If Yes, ____________________________________________________________________

________________________________________________________________________

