## Appendix P: Classification of Adverse Events

**CLASSIFICATION OF ADVERSE EVENTS**

Adverse Events (AE):

All observed or volunteered adverse events regardless of treatment group or suspected causal relationship to study drug will be recorded on the AE Form. All AE’s must be classified according to their severity as Mild, Moderate and Severe.

For all AE, the investigator must pursue and obtain information adequate both to determine the outcome of the adverse event and to assess whether it meets the criteria for classification as a Serious AE.

Follow-up of the adverse event even after the date of therapy discontinuation, is required if the AE or its sequelae persist. Follow-up is required until the event or its sequelae resolve or stabilize at a level acceptable to the Investigator.

*Please note that AE are not limited only to adverse drug reactions. Any noxious event and or a medically important deviations from normality will be recorded as AE.*

Criteria for determining category of relationship of AE to trial treatment will be as follows:

1. Not related: AE’s which are definitely attributed to other causes.

2. Unlikely: (must satisfy at least two)

- It does not follow a reasonable temporal sequence from administration of the test drug
- It could readily have been produced by the patients clinical state, environmental or toxic factors, or other modes of therapy administered to the patient
- It does not follow a known pattern of response to the test drug
- It does not reappear or worsen when the drug is re-administered

3. Possible: (must satisfy at least two criteria) An AE may be considered possibly related if or when

- It follows a temporal sequence from administration of the drug
- It could not readily have been produced by the patient’s clinical state, environmental or toxic factors.
- It follows a known pattern of response to the test drug

4. Probable: (must satisfy three of the following)

- It follows a reasonable temporal sequence from administration of the drug
- It could not be reasonably explained by the known characteristics of the patient’s clinical state, environmental or toxic factors, or other modes of therapy administered to the patient
- It decreases or disappears on cessation or reduction in dose.
- It follows a known pattern of response to the test drug

5. Definitely (must satisfy all four criteria)

- It follows a reasonable temporal sequence from administration of the drug

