- It could not be reasonably explained by the known characteristics of the patient’s clinical state, environmental or toxic factors, or other modes of therapy administered to the patient
- It decreases or disappears on cessation or reduction in dose and recurs with re-exposure to drug.
- It follows a known pattern of response to the test drug

f) Serious Adverse events (SAE):

All serious adverse events which occur during the study until the last follow-up visit required by the protocol, regardless of treatment group or suspected relationship to drug, must be reported immediately by telephone \ fax to Principal Investigator***,*** .

SAE include those that suggest a significant hazard, such as events which:

- are fatal
- result in permanent disability
- require in – patient hospitalization or a hospital stay
- are life – threatening
- a congenital anomaly or drug overdose

It should be emphasized that, regardless of the above criteria, any additional adverse experience which the investigator considers serious should be immediately reported.

For all serious adverse events, the investigator is obligated to pursue and provide information as requested, in addition to that on the case record form. In general, this will include a description of the adverse event in sufficient detail to allow for a complete medical assessment. The investigator should ensure that information on such cases is reported by telephone or by other means and information entered in the case record form is accurate and consistent.

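### The Adverse Event Form names Ashwagandha and hydroxychloroquine with Yes/No relatedness, so it has no field for Appendix P causality, or for per-event action taken, on the assigned Ayurvedic formulation

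*Combined protocol and SAP*

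**What the plan says.** The protocol covers three separate two-arm trials of AYUSH 64, Yashtimadhu or Samshamani Vati Plus added to standard of care (Explanatory Note; Sections 5 and 16).

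Section 14 has the study physician classify adverse events under Appendix P and the investigator record them, with a grade, on the AE form. Appendix P is explicit about scope: "All observed or volunteered adverse events regardless of treatment group or suspected causal relationship to study drug will be recorded on the AE Form". It introduces its causality scale with "Criteria for determining category of relationship of AE to trial treatment will be as follows" and then defines five categories: *Not related*, *Unlikely*, *Possible*, *Probable* and *Definitely*.

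The form itself, in Appendix Q, has one relatedness row that reads "Related to study treatment : Ashwagandha" and a second for hydroxychloroquine, each answered Yes or No. A further Yes/No row covers study procedures. It has an action-taken row for Ashwagandha and another headed "Action taken with study treatment: Hydroxychloroquine". Each offers dose unchanged, interrupted, withdrawn or not applicable. Below these is a separate row for other action, which includes a box for permanent discontinuation from the study that names no drug.

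**The concern.** Neither named drug is an investigational product here. Hydroxychloroquine could be part of a patient's standard of care, since Section 2.6 notes that national guidance mentions it. Ashwagandha has no role in any of the three trials, and the exclusion criteria bar patients on other Ayurvedic treatment. Completed literally, the Ashwagandha relatedness row reads No for every event in both arms, and no row exists for the product being tested.

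The form also cannot hold the classification that Section 14 and Appendix P ask for. Safety is part of the primary objective (Section 4), and drug-related side effects, toxicity and tolerability are a listed outcome (Section 11.2, item 8). If the event-level causality judgement is not written down when the event is assessed, it is hard to reconstruct later. In a multicentre study, each site could also improvise differently.

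**Working it through.** No sample size, power or error-rate figure bears on this point. The check sets the required record against the fields on the forms shown.

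**Step 1: what the AE form can hold.**

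| Item | Required or permitted by the plan | On the Appendix Q form |
| --- | --- | --- |
| Drug assessed | The assigned formulation, one of three (Section 16) | Ashwagandha, hydroxychloroquine |
| Causality | 5 categories (Appendix P) | 2 options, Yes or No |
| Change of dose | Allowed to the Ayurveda physician, with reasons documented (Section 3.1) | No box for a changed dose |
| Grade | 1 to 5 (Appendix R) | 1 to 4 |

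Drug-specific rows: 2 relatedness + 2 action = 4. Rows that name a formulation used in any of the three trials: 0 of 4. Rows with a blank for the assigned drug: 0.

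Splitting five ordered categories into Yes and No can be done at 5 − 1 = 4 points, and the plan does not say which applies. This shows only that the Yes/No answer is undefined relative to Appendix P; it does not measure any effect on results.

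**Step 2: whether another form shown fills the gap.**

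| Type of event | What is recorded elsewhere | What is missing |
| --- | --- | --- |
| Serious | Section 19.1 lists a "Serious Adverse Event Form", which is not shown | Cannot be judged |
| Non-serious, leads to withdrawal | Reason entered in the CRF (Sections 9 and 18.2); Appendix K lists reasons for stopping therapy | The Appendix P category |
| Non-serious, drug interrupted | Appendix K: Yes/No and two from/to date lines for the investigational drug, per patient | The Appendix P category and a link to the event |
| Non-serious, neither | The patient's own answer to "Did you Suffer from any symptom that could be due to the study drug" and a similar daily question in the mobile App (Section 19.3) | The Appendix P category and the action taken |

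No form shown (Appendices H, I, J, K, M, N, Q and S, and the Self-Reported Questionnaire) carries the five-category scale.

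**Step 3: whether this is a carry-over.** Section 17.2 describes the survival analysis as comparing HCQ with Ashwagandha, and Appendix O presents its laboratory tests as belonging to a prophylaxis protocol. Both fit a form brought across from another study. The rows are intact in the text, so extraction or redaction does not explain them.

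**Step 4: what the action row would add.** Appendix P requires for *Definitely* that "It decreases or disappears on cessation or reduction in dose and recurs with re-exposure to drug". *Probable* needs three of four criteria, one of which is improvement on stopping the drug or reducing its dose. An action row for the right drug would document the stop or reduction beside the event. It would not record whether the event then improved.

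**The case against.** The strongest reply is that the judgement is made and leaves traces even though the form is wrong. The study physician must classify each event under Appendix P. Section 18.3 requires every event to be noted in the patient's records. Drug-related toxicity is a listed reason for withdrawal, and the reason must go in the CRF. The third stop rule in Section 14 rests on the investigator's opinion that the intervention is the likely cause. Appendix K gives interruption dates that could often be matched to event dates. The Termination Form and Medication Log (Section 19.1) and the SOPs (Section 19.12) are not shown and might tell sites what to write. The only adverse-event analysis specified, in Section 17.2, compares the proportions of patients with an event and uses no causality category.

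Most of this stands, and it rules out four stronger readings that a reader might infer:

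- That no form records any action on the assigned drug. Appendix K does, per patient, and Appendix Q has its drug-neutral discontinuation box.
- That the patient's opinion is the only attribution held. Withdrawals for toxicity carry the investigator's view.
- That sites have no instruction. The documents shown contain none, but the SOPs cannot be checked.
- That the between-arm comparison of event proportions is compromised. It needs no causality field.

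The dechallenge argument is also limited. Nothing in the plan says that the action row is used to assign the category, and *Probable* can be reached without it.

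What does not stand is the idea that these traces replace the field. A general duty to note events in the records, a reason for withdrawal and a pair of interruption dates do not give one of five categories for each event.

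**Conclusion.** The point holds in this form: the AE form has no field for the Appendix P causality category, or for the per-event action taken, for the assigned formulation. None of its 4 drug-specific rows names a trial product, and it offers 2 relatedness options where 5 categories are required.

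The practical gap is mainly non-serious events that do not lead to withdrawal. For these, the forms shown leave drug-related side effects and toxicity without a properly recorded investigator judgement. How many events that would be cannot be estimated from the documents. The comparison of event proportions between arms is untouched.

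This is an error on an operative form, worth correcting but no threat to the trials' efficacy comparison or overall event counts. The conclusion assumes that Appendix Q is used as printed and that no SOP or form not shown corrects it.

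**What to change.** Revise the one page of Appendix Q:

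- Replace the Ashwagandha rows with: Assigned Ayurvedic formulation (name; or none, SOC arm).
- Replace the hydroxychloroquine rows with: SOC drug (name).
- For each, replace Yes/No relatedness with *Not related / Unlikely / Possible / Probable / Definitely*, as defined in Appendix P.
- Add a dose-changed option to the action rows, because Section 3.1 allows dose changes and Appendix P uses dose reduction.
- Add a Grade 5 box, to match Appendix R.

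Check that the serious-event form uses the same drug names and categories.

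The cost is one corrected form page before first use, with no added visits, procedures or patients.

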**Appendix R: Grading of Adverse Events**

**GRADING OF ADVERSE EVENTS**

| Grade | Adjective | Description |
| --- | --- | --- |
| Grade 1 | Mild | Asymptomatic or mild symptoms ; clinical or diagnostic observations only ; intervention not indicated. |
| Grade 2 | Moderate | Local or non-invasive intervention indicated; limiting age - appropriate instrumental ADL |
| Grade 3 | Severe | Severe or medically significant but not immediately life - threatening; hospitalization or prolongation of hospitalization indicated; disabling; limiting self -care ADL |
| Grade 4 | Life Threatening | Urgent intervention indicated |
| Grade 5 | Death | Death related AE |

## Appendix S: Patient Information Card

**AYUSH COVID-19 PATIENT PROTOCOL 2020**

**PATIENT INFORMATION CARD**

Patient No _____________ Patient Initials: _____________ ___

**PLEASE CARRY THIS CARD WITH YOU AT ALL TIMES**

THIS PATIENT IS PARTICIPATING IN A CLINICAL TRIAL

A Randomized, Open Label, Parallel Efficacy, Active Control, Multi-Centre Exploratory Drug Trial to Evaluate Efficacy and Safety of an Ayurvedic Formulation as Adjunct Treatment to Standard of Care for the Management of Mild to Moderate COVID-19 patients

***INSTITUTION NAME:__________________________________________________________***

***______________________________________________________________________________***

***INSTITUTION ADDRESS:_____________________________________________________***

***____________________________________________________________________________________________________________________________________________________________***

***EMERGENCY 24 HOUR PHONE :_______________________________________________***

PRESCRIPTION ON DISCHARGE:

## Appendix T: Declartion of Helsinki

**
[figure not shown]
**

**
[figure not shown]
**

**
[figure not shown]
**

**
[figure not shown]
**

**
[figure not shown]
**

